#### 4.7 Randomisation and blinding

Articles, which meet the eligibility criteria as a primary report of an RCT, for which the journal decides to send out for external peer review will be randomised into one of the two groups (allocation 1:1). The randomisation list will be created by the study-randomizer system (43) using random block sizes between 2 and 8 and stratification by journal. As soon as the first peer-reviewer accepts the invitation, the manuscript will be included and randomised to one of the two intervention arms. One of the investigators (BS) will log onto the study randomizer-system (43) entering the study identification number (ID; provided from the Journal), the study title, as well as the journal the study was submitted to. Subsequently, all additional peer-reviewers accepting the invitation to review the same manuscript will receive the same intervention (C-short plus usual practice or usual practice only) as the first peer-reviewer.

Authors will be blinded to the intervention allocation. Editors will not be actively informed about the randomisation (possible exception listed under “4.3 Interventions”). To avoid potential bias, peer reviewers and manuscript authors will not be informed of the study hypothesis, design and intervention.

Outcomes will be assessed in duplicate (see assessment of outcomes). At least one outcome assessors will be blinded. Due to restricted resources it might be possible that the investigator conducting the randomisation (BS) will be included in the data-extraction from published manuscripts.

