#### 4.3 Interventions

#### Experimental group: C-short plus usual practice

After accepting to review an article, peer reviewers will receive the automated, journal specific standard email with general information as per each journal's usual practice (e.g. where to access the manuscript, date when the peer review report is due). In addition, peer-reviewers who received a manuscript which was randomised to C-short will receive an additional email including a short version of the CONSORT checklist (C-short) (either within the email or as an attachment; based on the preferences and possibilities of the journal) focusing on the 10 most important and most poorly reported items (Table 1; as previously defined by a group of experts of the CONSORT Group (38)). Peer-reviewers will be asked to pay particular attention to items in the C-short checklist and request authors to report on these items, if not already adequately reported. This second email, containing the C-short checklist, is not generated automatically within the existing journal editorial management system (e.g. ScholarOne or Editorial Manager); it will be sent by the investigator who has access to the journal editorial system (BS). An example of this additional email is presented within the appendix (appendix 1; the exact wording might be changed according to the preferences of the participating journals). At least twice a week the editorial management system will be checked for each journal and if a peer reviewer has accepted an invitation to review, an email containing the C-short intervention will be generated and sent. It might be possible that some journals will only provide the right to access and read manuscripts in the editorial management system, but not to send emails. If this is the case, the corresponding Editor (or designated person within the journal) will be informed to send the emails.

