### Data collection methods:

The outcomes will be assessed independently by two (blinded or at least partially blinded; see “blinding”) outcome assessors with expertise in the design and reporting of clinical trials. Any disagreement will be resolved by consensus or if necessary by consulting a third assessor. To ensure consistency between reviewers, we will first pilot the data extraction form; any disparities in the interpretation will be discussed and the data extraction form will be modified accordingly.

Adequate reporting of items will be assessed from published full-text publications adhering to the CONSORT C-short checklist (21). The following included items have sub-items which will be extracted separately:

- Outcomes (item 6a): (i) Define primary outcome, (ii) how it was measured, (iii) at what time point, and (iv) the analysis metric (e.g. change from baseline, final value).
- Sample size (item 7a): (i) The estimated outcomes in each group, (ii) the  $\alpha$  (type I) error level, (iii) the statistical power (or the  $\beta$  (type II) error level), (iv) for continuous outcomes, the standard deviation of the measurements
- Blinding (item 11a): Is the blinding status clear for the following persons: (i) Healthcare provider, (ii) patients, and (iii) outcome assessors.
- Funding (item 25): (i) The funding source, and (ii) the role of funder in the design, conduct, analysis, and reporting.

All items will be judged as either “yes” meaning adequately reported, “no” meaning not adequately reported, or “NA” meaning that this sub-item is not applicable for this RCT. Items with different sub-items will only be judged as adequately reported if all relevant sub-items were adequately reported.

- Time from assigning an academic editor until the first decision: The day when the academic editor was assigned and the day of the first decision (e.g. major revision, minor revision, rejected) will be extracted to calculate the number of days until the first decision.
- Proportion of articles directly rejected after the first round of peer-review: Articles which were not invited for re-submission will be labelled and counted.
- Proportion of articles published: Articles which will be published will be counted and collected for data extraction.

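### If the randomising investigator also extracts data, the consensus rule could let knowledge of the arm affect the primary score on items where the two assessors disagree

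*Protocol*

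**What the plan says.** Protocol section 4.4 (Data collection methods) has two assessors score each published article: "The outcomes will be assessed independently by two (blinded or at least partially blinded; see" the blinding section. Each item is rated yes, no or not applicable, with yes "meaning adequately reported". An item with sub-items counts as adequate only if every relevant sub-item does. On differences between assessors it says: "Any disagreement will be resolved by consensus or if necessary by consulting a third assessor". Whether that third assessor is blinded is not stated.

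Section 4.7 (Randomisation and blinding) sets the minimum: "At least one outcome assessors will be blinded". It then adds: "Due to restricted resources it might be possible that the investigator conducting the randomisation" "will be included in the data-extraction from published manuscripts".

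Section 4.3 (Experimental group) shows what that investigator knows. Of the additional email carrying the checklist it says that "it will be sent by the investigator who has access to the journal editorial system", and this is the same investigator who randomises. Where a journal gives no sending rights, "the corresponding Editor (or designated person within the journal) will be informed to send the emails". The investigator still randomises in that case, so still learns the arm.

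**The concern.** The primary outcome is the mean proportion of ten items judged adequate. One of the two people judging may have entered the manuscript's title into the randomisation system, seen its allocation and emailed its peer reviewers. No step is described that would hide the article's identity at scoring, and a published title can be recognised or looked up.

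Independent duplicate rating with one blinded rater deals with this only up to the point of disagreement. After that, the two raters confer. Nothing excludes the unblinded one from the discussion, makes the blinded rating decisive, or requires that a third assessor be blinded. At stake is detection bias in the primary outcome, confined to the contested items. The all-or-nothing rule adds leverage: one sub-item decided differently changes a whole item, which is 0.10 of an article's score when all ten items apply.

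**Working it through.** **The plan's own figure.** Section 4.6, scenario 2: 71% v 82%, SD 0.25, two-sided 5%, 83 per arm, 80% power.
- Standard error of the difference: 0.25 × √(2/83) = 0.0388, or about 3.9 percentage points.
- Noncentrality: 0.11 / 0.0388 = 2.83. With 164 degrees of freedom the t-test has power 80.5%. The stated figure is reproduced and is not in dispute.

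**Where allocation knowledge can enter.**

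| Situation for an item | Value analysed | Protected by the blinded rating? |
|---|---|---|
| Both assessors agree | the common rating | yes |
| They differ, consensus reached | agreed after discussion that may include the unblinded investigator | only partly: the blinded assessor must assent |
| They differ, third assessor consulted | outcome of that consultation | not assured: blinding of the third assessor is not stated |

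**How large it could be.** The protocol gives no disagreement rate and no measure of assessor influence, so both are assumptions here. Write the shift in the between-arm difference as

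b = (share of item ratings in disagreement) × (net share of those settled in favour of C-short because the arm is known).

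With no true effect, the chance of p < 0.05 comes from a noncentral t distribution with 164 degrees of freedom and noncentrality b / 0.0388.

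| Assumed disagreement × net tilt | Shift b (points) | b / 0.0388 | Share of planned 11 points | Type I error |
|---|---|---|---|---|
| 5% × 10% | 0.5 | 0.13 | 5% | 5.2% |
| 10% × 10% | 1 | 0.26 | 9% | 5.8% |
| 15% × 20% | 3 | 0.77 | 27% | 12% |
| 15% × 30% | 4.5 | 1.16 | 41% | 21% |

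The low rows are negligible and the high rows are not. The documents do not say which applies. A tilt away from C-short, for instance from over-correction by an investigator aware of the risk, would instead pull the estimated effect down.

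**Workload of the fix.** 166 articles × 10 items = 1,660 item ratings. At 10% to 20% disagreement, 166 to 332 items would go to the third assessor. Counting sub-items separately raises this: section 4.4 lists 4 + 4 + 3 + 2 = 13 sub-items, which with the six undivided items makes 19 ratings per article, or 19 × 166 = 3,154 in all. The same rates then give about 315 to 631.

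**The case against.** The protocol discloses the arrangement openly, gives a resource reason, and words it as something that may happen. Sections 4.4 and 4.7 agree with each other, and no stated figure is wrong. There are real safeguards: two independent assessments by people with expertise in trial reporting, a piloted form, at least one blinded assessor, and a third if needed. Several items are close to presence checks (registration, protocol location, funding source). The bias also depends on the investigator remembering or looking up the arm after publication. All of this stands, and it narrows the point to contested judgement items in a case that may not occur.

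A reader might infer that the single blinded rating gives the analysed value no protection. The text does not support that. Wherever the assessors agree, which is 80% to 95% of ratings across the disagreement rates assumed here, the analysed value equals the blinded rating. Elsewhere, consensus still needs the blinded assessor's assent.

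It can also be said that a sensitivity analysis and the retention of raw ratings belong in an analysis plan, which is not at hand. Their absence from the protocol is therefore not the fault. Who scores and who adjudicates, however, is a conduct rule that the protocol itself sets. It has to be right before extraction starts, because independent ratings that were not kept cannot be recovered.

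**Conclusion.** The point holds as a conditional weakness in the adjudication rule. If the randomising investigator extracts, the protocol lets a person who knows the arm take part in settling the contested items of the primary outcome, and it does not assure a blinded third assessor. The items most exposed are outcomes, blinding, effect estimation and harms.

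It would be tempting to conclude that the primary result will be biased towards C-short. The documents do not support that: neither direction nor size can be derived from them. The range of 5.2% to 21% for the type I error rests on assumed shifts of 0.5 to 4.5 points, no true effect, SD 0.25 and 83 articles per arm. The sample size is unaffected. The correction is worth making because it is cheap and is needed before extraction begins.

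**What to change.** Amend sections 4.4 and 4.7 (Randomisation and blinding) as follows, to apply if the randomising investigator is one of the two extractors:

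1. That person takes no part in resolving disagreements. These go directly to the third assessor already foreseen, who is blinded to arm and does not discuss the article with that person.
2. Both assessors' independent ratings are recorded and stored before any resolution.
3. A sensitivity analysis of the primary outcome, using only the blinded assessor's independent ratings, is pre-specified in the protocol or the statistical analysis plan.

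The cost is wording, one extra analysis and third-assessor time for roughly 166 to 332 item-level disagreements if 10% to 20% of items differ. That is a real burden given the stated resource limits. If the time cannot be found, steps 2 and 3 alone cost almost nothing and still yield an estimate of the primary outcome free of the unblinded assessor's influence. That estimate rests on a single rater, so it should be read beside the main analysis and not in place of it.

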#### 4.7 Data management and confidentiality

Outcomes from publications will be assessed and extracted in duplicate. Since this information is not confidential, we will use Google Forms for data extraction from published RCTs. Data entered will be validated for completeness.

Data from the editorial manager software (e.g. Title of manuscript, first author, randomisation ID, Journal, date when manuscript was accepted by and academic editor, date when the final decision was made, final decision, number of peer-reviewers who peer reviewed the manuscript, the peer review) will be extracted, anonymised and entered in a password protected database which is saved on a server from the University of Oxford. Data will be managed and curated according to University of Oxford regulations, which includes regular back-up (on a daily basis) of the virtual drives where the data are stored.

The raw data extracted from the included manuscripts can be made openly accessible in an anonymised way (i.e. giving the included RCT a number instead of identifying them). Derived/aggregated data, including anonymised information generated from the journals' editorial manager software, will be stored and made available to the research community when the project ends (see also "8. Publication policy and access to data"). Where appropriate, the researcher who has access to the editorial manager software (BS) and anyone else who will see the identifiable data will sign a confidentiality agreement with the participating journals, confirming that they will not share identifiable data with any other party. Journals such as the BMJ series state in their Company Privacy Statement that research programmes for quality improvement might be in place. Furthermore, peer reviewers for all BMJ journals receive the following statement in their invitation letter *"We are constantly trying to find ways of improving the peer review system and have an ongoing programme of research. If you do not wish your review entered into a study please let us know by emailing [...] as soon as possible."*

## 4.8 Statistical methods

### 4.8.1 Populations of analysis

The main population for analysis will be all manuscripts randomised and accepted for publication in the participating journals. Differently from RCTs conducted with patients, where drop outs need to be carefully considered (e.g. multiple imputation of missing data), we are only interested in the reporting adherence of RCTs that are published. All outcomes will be calculated based on the main population for analysis. The secondary outcome "Time to the first decision", will additionally be calculated considering all randomised manuscripts (including the ones which were not published).

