## **2. Hypothesis**

We propose an RCT to evaluate the impact of asking peer reviewers to use a short version of the CONSORT checklist when reviewing a manuscript of an RCT and whether it improves the completeness of reporting. Our hypothesis is that reminding peer reviewers of the CONSORT items (including a short explanation of those items) will result in higher adherence to CONSORT guidelines in published RCTs. We only selected a limited number of the CONSORT items because we did not want to deter peer reviewers with too much information. Since peer reviewing in general can be burdensome, we felt that this approach is more promising than listing all items, risking that the information will be ignored. The short version of the CONSORT checklist is based on the same items described in a previous study as the 10 most important and underreported CONSORT items (38).

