#### 4.8.3 Analysis of primary endpoint

The primary outcome will be the difference of the mean proportion of adequately reported items of the 10 most important and poorly reported CONSORT items. If the data on the primary outcome is normally distributed then the two groups (i.e. C-short plus usual practice vs. usual practice) will be compared using an unpaired Student's t-test to compare the unadjusted mean proportion of adequate reporting. If the data is not normally distributed, comparisons will be performed using a non-parametric equivalent test (i.e. Wilcoxon-Mann-Whitney test for testing whether the population medians of the two groups are the same).

For the analyses of the primary outcomes a p-value of 0.05 (5% significance level) will be used to indicate statistical significance and treatment effect (mean difference) reported with 95% confidence intervals (or median and respective interquartile ranges, in case of asymmetric distribution). Exact p-values will be presented up to three decimal places. We anticipate there will be no missing data in this study, neither at the individual C-short items, nor at the manuscript level. This is due to the study design, which will include only the randomised manuscripts that are accepted for publication.

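### The primary comparison is restricted to published manuscripts, a status decided after randomisation, and the same restriction, read literally, disables the two outcomes that could show differential selection

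*Protocol*

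**What the plan says.** - **Randomisation** (section 4.7, Randomisation and blinding): "As soon as the first peer-reviewer accepts the invitation, the manuscript will be included and randomised to one of the two intervention arms".
- **Intervention** (section 4.3): "Peer-reviewers will be asked to pay particular attention to items in the C-short checklist", and to ask authors to supply what is missing. These ten items are also the ones scored for the primary outcome.
- **Analysis population** (section 4.8.1): "The main population for analysis will be all manuscripts randomised and accepted for publication in the participating journals". The reason given is that, unlike in patient trials, "we are only interested in the reporting adherence of RCTs that are published".
- **Scope of that population** (section 4.8.1): "All outcomes will be calculated based on the main population for analysis". Only time to first decision is also calculated on all randomised manuscripts.
- **Missing data** (section 4.8.3): "We anticipate there will be no missing data in this study, neither at the individual C-short items, nor at the manuscript level". This is attributed to a design "which will include only the randomised manuscripts that are accepted for publication".
- **Secondary outcomes** (section 4.4): these include the proportion directly rejected after the first review round and the proportion published, both taken from the editorial software.
- **Recruitment** (section 4.6): it continues until 83 articles per arm are published. Manuscripts published more than three months after recruitment stops are excluded.

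**The concern.** Between randomisation and entry into the analysis set, the intervention acts on reviewers, whose reports inform the journal's decision. They are prompted on exactly the items that are later scored, so entry into the analysis set may depend on arm and on reporting quality together. If C-short leads to the loss of more poorly reported manuscripts, the published C-short articles score higher even if no manuscript was improved. If it helps weak manuscripts through revision to acceptance, the published C-short set contains more of them and a real benefit is diluted. Recruiting to 83 published per arm equalises the numbers, not the composition.

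At stake is the attribution of the result. Section 2 asks "whether it improves the completeness of reporting". A set that was filtered and a set that was improved can give the same primary estimate.

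The protocol's natural safeguard is to compare rejection and publication by arm. The population sentence in section 4.8.1, taken as written, removes it.

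**Working it through.** **1. The plan's own figure.** Inputs from section 4.6, scenario 2: 0.71 against 0.82, SD 0.25, two-sided 5%, power 80%. The normal approximation gives 2 × (0.25 × (1.960 + 0.842) / 0.11)² = 81.1, so 82 per arm. The exact t-test gives 82.05, so 83 per arm, as stated. The target difference is 11 points and the standard error is √(2 × 0.0625 / 83) = 0.0388, or 3.9 points.

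**2. The two outcomes under section 4.8.1.** Among manuscripts accepted for publication, none was directly rejected and nearly all are published (the exception is one that appears after the three-month cut-off). The proportions are then 0% and about 100% in both arms by construction. This does not fit section 4.4, where both are outcomes to be compared.

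**3. Size of a purely selective shift.** The protocol gives no rejection or publication rate, so two quantities are assumed:
- q, the share of otherwise publishable manuscripts additionally lost under C-short. For example, publication of 50% falling to 45% gives q = 10%.
- ρ, the correlation between the tendency to be lost and poor reporting.

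With no true effect on reporting, shift = ρ × SD × φ(z_q) / (1 − q). For q = 0.10: z = −1.2816, φ = 0.1755, and 0.1755 / 0.90 = 0.1950. At ρ = 1 this gives 0.25 × 0.1950 = 0.0487.

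Two variants were also run:
- A score bounded between 0 and 1 (beta distribution, mean 0.71, SD 0.25) with the lowest 10% removed.
- Random loss of 20% within the lower half, which is 10% overall. The halves lie 0.1995 either side of the mean and the lower half's weight falls to 0.8 / 1.8 = 0.444, so the shift is 0.1995 × (1 − 2 × 0.444) = 0.022.

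False significance is the rejection probability of the two-sided t-test with 83 per arm at that shift, keeping SD 0.25 in both arms.

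| Selection at q = 10% | Shift (points) | Share of 11 points | False significance |
|---|---|---|---|
| ρ = 0.3 | 1.5 | 13% | about 7% |
| Random within lower half | 2.2 | 20% | about 9% |
| ρ = 0.5 | 2.4 | 22% | about 10% |
| ρ = 0.7 | 3.4 | 31% | about 14% |
| Strictly the worst, normal | 4.9 | 44% | about 24% |
| Strictly the worst, bounded | 5.6 | 51% | about 30% |

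With strict selection, q = 5% gives 2.7 to 3.0 points and q = 20% gives 8.8 to 10.2. With ρ = 0.3 the same losses give 0.8 and 2.6 points.

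**4. What it takes to reach half the target (5.5 points).** Under the normal model, q must be about 11.5% at ρ = 1, 18% at ρ = 0.7, 26% at ρ = 0.5 and 46% at ρ = 0.3.

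**5. Would a comparison of publication reveal it?** Assume 40% to 70% publication in the control arm and enough manuscripts randomised to yield 83 published under C-short. For 50% falling to 45%, that is 83 / 0.45, or 185 per arm, with power of about 16%. Across 40% to 70% and relative drops of 10% to 15%, power is about 14% to 45%. A non-significant comparison would not be reassuring.

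**The case against.** **The journal decides, not the reviewers.** A reader might infer that the reviewers who receive C-short determine publication. The protocol does not support that: Table 2 refers to the journal's decision, and editors are not actively told the allocation, except where a journal sends the emails itself. C-short asks reviewers to request better reporting, which invites revision rather than rejection. This stands, and it makes the pathway indirect. It does not close it, because the reports inform the decision and the protocol itself lists rejection and publication as outcomes.

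**Published RCTs are the stated target.** Sections 2 and 3.1 both name reporting in published RCTs. For a journal considering C-short, a better published output is a legitimate aim, and filtering may be part of it. This also stands, and it is why the published-article comparison should remain primary. It does not license attributing the difference to improved manuscripts.

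**Selection alone could produce half the target effect.** A reader might draw this from the upper rows of the table. No figure in the protocol supports it as an expectation. It needs about 10% to 12% extra loss taken strictly from the worst-reported manuscripts. Rejection acts on the submitted version while scoring uses the published one, so selection that sharp is unlikely.

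**A sensitivity analysis may be in the SAP.** The SAP is not shown, so its absence from the protocol is not the defect. The defect is what section 4.8.1 fixes: the argument that drop-outs need no care, and a population rule that empties two outcomes of information.

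**The missing-data sentence is conditional.** It is true among published manuscripts. It misleads only when read as covering all randomised manuscripts.

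**Conclusion.** The concern holds as a fault in section 4.8.1, of moderate weight. The primary estimate can stay, but as planned it is a difference among published articles, and the arms within that set are not protected by randomisation. The population sentence, read literally, also prevents the rejection and publication outcomes from showing differential selection.

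The size cannot be derived from the protocol. With SD 0.25, no true effect and an assumed 10% relative drop in publication under C-short, the spurious shift is about 1.5 points for weak selection (correlation 0.3) to 4.9–5.6 points if strictly the worst-reported are lost. False significance is about 7% to 30% instead of 5%. The top of that range is near the worst case. If C-short instead helps weakly reported manuscripts get accepted, the bias runs the other way. That selection will occur, or that a positive result would be mostly artefact, is not shown.

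**What to change.** 1. Keep the published-article comparison as the primary analysis.
2. Amend section 4.8.1 so that direct rejection and publication are calculated on all randomised manuscripts, as is already done for time to first decision. Show both by arm beside the primary result, with confidence intervals, given the low power in step 5 of the working.
3. Add a trimming-bounds sensitivity analysis. In the arm with the higher publication proportion, trim the excess share of published articles, once from the best-reported and once from the worst-reported end, and give both mean differences. Count manuscripts still undecided or unpublished at the section 4.6 cut-off separately from rejections, so that administrative timing is not treated as selection.
4. Describe the primary result as a difference among published articles, and discuss the bounds before attributing it to improved manuscripts.
5. Qualify the sentence in section 4.8.3 to say that no data are expected to be missing among published manuscripts only.

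The cost is one extra analysis and a few sentences. Final decisions are already to be extracted from the editorial systems. The bounds may be wide if publication differs between arms, and they assume that selection acts in one direction.
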